### Sample size {14}

The sample size calculation is based on detecting a difference of 20% between the intervention group and the remaining cohort achieving a sustained return to work (1:3 allocation ratio). Assuming a cohort return to work rate as high as 10%, with a power of 80% and a 5% significance level, we will need data on 176 participants (132 control and 44 intervention) [13]. Allowing for a 20% loss to follow-up and a crude 14% inflation in the intervention group for an estimated design effect due to clustering by the case manager (assumptions here are an ICC of 0.01, smallest cluster size of 7 and largest of 16, and so a design effect of 1.14), we will aim to recruit 228 people [59]. If a 1:3 ratio allocation provides insufficient throughput for us to regularly form small groups of people for the work preparation session due to the proportion of people not accepting the intervention being high, we may switch to target overall balanced randomisation (1:2). In this case, our overall required sample size will be reduced to 190 in total, with the above inflations (with the same assumptions the estimated design effect will be 1.11 in this case) [59].

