### Recruitment {15}

Over an anticipated recruitment period of 1 year, we will mount an advertising campaign across social media, pain groups, and charities (including pain and rheumatological charities: *Ryggforeningen*, *Norsk Revmatikerforbund*, *Foreningen for Kroniske smerter*), public facilities, and *Frisklivssentralene* (i.e. ‘healthy living’ centres, which provide help with health and work matters). Manpower will aid recruitment using its online channels. We will offer NOK 200 of high street vouchers to those joining the cohort, which we have previously found to help recruitment [60, 61].

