### Statistical methods

#### Statistical methods for primary and secondary outcomes {20a}

A detailed statistical analysis plan has been finalised and agreed prior to analysis by the research team. We will report all participant flow in line with the CONSORT guideline extension for reporting RCTs conducted using cohorts and routinely collected data showing withdrawal and loss to follow-up [15]. Analyses will be conducted within TSD using Stata v17 or above (Stata Corporation, College Station, TX). Participant characteristics and outcomes will be summarised as mean and standard deviation for normally distributed continuous data or with median and ranges for data with skewed distributions or counts and percentage for categorical data. The primary analysis approach will be ‘intention-to-treat’. To account for the trial design featuring clustering in the intervention arm, generalised linear (GLM) mixed effects models will be used to estimate the between-group differences for both primary and secondary continuous outcomes, adjusting for age, gender, and duration of pain, with a random intercept for case manager. For example, we will analyse the between-group differences in sustained return to work (a binary outcome) using a generalised mixed-effect model with logit link function, the above covariates, and fitting a random effect in case manager allocation.

Secondary outcomes will also be analysed using generalised mixed models, using link functions appropriate to the outcome (e.g. where outcomes are continuous, we will use a canonical link function). In all cases, we will adjust for the same covariates (i.e. age, gender, and duration of pain). The adjusted treatment effect estimates (mean difference) between the groups will be presented as point estimates within a 95% confidence interval. Our outcome measures are largely independent and no correction for multiple testing will be done. *P*-values < 0.05 will be considered statistically significant. All tests will be two-sided.

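### If the permitted mid-recruitment change of allocation ratio is used, part of any drift in return-to-work rates enters the treatment effect, because the fixed covariate list has no term for allocation phase

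*Protocol article*

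**What the plan says.** Under Sample size {14}, the protocol article plans on "detecting a difference of 20% between the intervention group and the remaining cohort achieving a sustained return to work (1:3 allocation ratio"). If too few people accept the intervention to form the small groups, "we may switch to target overall balanced randomisation (1:2"), and the total falls from 228 to 190. The section on blinding {17a} likewise treats the outcome of a switch as balanced groups.

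Under Sequence generation {16a}, minimisation uses gender and age group, with a two-thirds probability for the favoured arm. Under Statistical methods {20a}, the models are specified as "adjusting for age, gender, and duration of pain, with a random intercept for case manager", and the same three covariates are carried to every secondary outcome. No section names a term, stratum or separate analysis for the period before and after a change of ratio. Under Recruitment {15}, enrolment runs "Over an anticipated recruitment period of 1 year", and the Trial design section allows pre-pilot participants to be included under conditions.

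**The concern.** Within each phase the comparison is randomised. Pooling two phases with different allocation ratios, without a term for phase, loses part of that protection: the intervention arm then holds proportionally more late recruits than the control arm. If late recruits would have returned to work more often anyway, the intervention looks better than it is; if less often, a real benefit is partly hidden. The protocol authorises the switch in advance and gives it its own sample size and design effect, yet the analysis is written as if the ratio never changed.

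**Working it through.** **Inputs from the protocol article.** Control rate 10% ("Assuming a cohort return to work rate as high as 10" per cent); difference 20 points, so 30% against 10%; "with a power of 80% and a 5% significance level"; "All tests will be two-sided"; loss to follow-up 20%; design effect on the intervention arm 1.14, or 1.11 after a switch; totals 228 and 190. **Assumptions, not in the document:** timing of the switch, size of the drift, and the allocation probability after the switch.

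**Step 1: reproduce the plan's figures.** A two-proportion calculation with continuity correction and three controls per intervention participant gives 44 + 132 = 176, matching "we will need data on 176 participants (132 control and 44 intervention"). Inflated: (132 + 44 × 1.14)/0.8 = 227.7, so 228. With equal arms the same method gives 72 per arm, and (72 + 72 × 1.11)/0.8 = 189.9, so 190. With two controls per intervention participant it gives 51 + 102, and (102 + 51 × 1.11)/0.8 = 198.3. The stated 190 is therefore reproduced by equal final arms and not by a literal 1:2.

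**Step 2: consequence for later allocation.** Equal final arms after a control-heavy start require more than half of later recruits to go to the intervention. If the later phase were only plain 1:1, late recruits would still be over-represented in the intervention arm, by less.

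**Step 3: fraction of drift carried.** With no true effect,

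bias in risk difference = drift × (late share of intervention arm − late share of control arm).

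For 190 recruits and a switch after 95:

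| Early phase offered | After the switch | Early (int./control) | Late (int./control) | Fraction carried |
|---|---|---|---|---|
| 25% | overall balance (75% offered) | 23.75 / 71.25 | 71.25 / 23.75 | 0.75 − 0.25 = 0.50 |
| 25% | two-thirds offered | 23.75 / 71.25 | 63.3 / 31.7 | 0.73 − 0.31 = 0.42 |
| 25% | plain 1:1 | 23.75 / 71.25 | 47.5 / 47.5 | 0.667 − 0.40 = 0.27 |
| one in three | overall balance (two-thirds offered) | 31.7 / 63.3 | 63.3 / 31.7 | 0.667 − 0.333 = 0.33 |
| one in three | plain 1:1 | 31.7 / 63.3 | 47.5 / 47.5 | 0.60 − 0.43 = 0.17 |

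Both starting fractions are shown because the sample size uses 44 of 176 (25%), whereas the Abstract, Trial design, consent and Participant timeline sections say one in three.

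**Step 4: in percentage points.** A 6-point drift gives 0.17 × 6 = 1.0 to 0.50 × 6 = 3.0 points. A 10-point drift gives 1.7 to 5.0 points. Moving the switch to 25% or 75% of recruitment widens the carried fraction to between 0.13 and 0.57.

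**Step 5: effect of a phase term.** Logistic models were simulated under no treatment effect: 152 evaluable participants (190 × 0.8), switch at the midpoint, 25% offered early, 3,000 runs per scenario, without the other covariates or a case-manager effect.

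| After the switch | Background rate | Median OR / type I error, no phase term | Median OR / type I error, with phase term |
|---|---|---|---|
| overall balance | 10% then 10% | 1.00 / 3.6% | 1.00 / 4.4% |
| overall balance | 10% then 15% | 1.26 / 6.2% | 1.00 / 4.3% |
| overall balance | 10% then 20% | 1.49 / 12.1% | 1.00 / 4.5% |
| overall balance | 10% then 5% | 0.69 / 4.9% | 1.00 / 4.0% |
| plain 1:1 | 10% then 20% | 1.23 / 6.5% | 1.00 / 4.5% |

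In the remaining plain 1:1 scenarios the median odds ratio with the phase term was 1.00, except for 10% then 5%, where it was 0.93 (0.82 without the term).

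**The case against.** The switch is optional and is triggered by acceptance and throughput, not by outcome data. A finalised statistical analysis plan is mentioned but not shown, and it may already contain a phase term. The document gives no evidence of drift: every participant has a 12-month window covering all seasons once, one recruitment campaign is described without sequencing of channels, and pre-pilot participants are included only if there has been no substantial amendment. A doubling of the background rate within a year is a strong assumption; at a 5-point rise the simulated type I error is 6.2%.

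Most of this stands as a limit on size and likelihood. It does not remove the point. Confounding by phase needs only unequal ratios and drift, whatever triggered the switch. Nor is the protocol silent in a way that leaves the matter open: it states a definite covariate list for all models, and that list does not cover a switch that the same protocol authorises.

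A reader might infer that any drift turns wholly into a false effect, or that arm and calendar period become inseparable. The documents do not support that. Unless the switch comes so late that all remaining recruits must be offered the intervention, both arms are recruited in both phases, and only a fraction of the drift is carried. A reader might also conclude that allocation must restart at a constant 1:1. That is not needed for validity, since the phase term removed the bias in simulation even when overall balance was pursued. A 1:1 restart would also leave the arms near 71 and 119 at a midpoint switch (23.75 + 47.5 and 71.25 + 47.5), against the equal arms behind 190 and the balance on which statistician blinding depends.

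**Conclusion.** The point holds conditionally. If the ratio is changed during recruitment and background return-to-work rates differ between phases, the models as listed give a biased pooled estimate in the direction of the drift for the intervention. At a midpoint switch about 0.17 to 0.50 of the drift is carried: about 1 to 3 points for an assumed 6-point drift and about 2 to 5 for an assumed 10-point drift. The upper figure is a quarter of the 20-point planned effect and requires the background rate to double, a 25% early phase, and overall balance reached afterwards. Drift size, switch timing and later probability are all assumptions. The issue is modest in most scenarios, but cheap to prevent before outcome data exist.

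**What to change.** In Sample size {14} and Statistical methods {20a}, state that if the allocation ratio changes, allocation phase (before or after the switch) is included as a fixed effect in the primary model and in all secondary models, alongside the covariates already listed. In Sample size {14}, also state the allocation probability that will apply after the switch. The cost is one degree of freedom and two sentences. If there is no switch, the term is not used and nothing changes.

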#### Intervention description {11a}

First, we will train two to four people with prior experience of working with pain patients (e.g. nursing, manual/occupational therapy, or psychology) to function as case managers for participants and identify obstacles to return to work using the ‘Psychosocial Flags Framework’ and a set of stem questions [13, 18]. Using a biopsychosocial approach, the case managers will identify and create a plan to tackle obstacles across personal, workplace, and social domains, documenting these in a return-to-work plan. Case managers will receive training on how to do this using a toolkit used as the evidence base for case management and for conducting work familiarisation sessions. Case managers will also receive training on pain management strategies and the Norwegian benefits system, as they will be unaffiliated with the Norwegian Labour and Welfare Administration (NAV), which our user input suggests may be important.

The trained case manager will contact participants by phone to make an initial assessment, explore work aspirations and skills, and help the participant to identify work obstacles. A face-to-face or video will be offered if the case manager considers one needed. Through collaboration with Manpower, a large recruitment company in Norway, the case manager will match the participant with a placement, based on skills, aspirations, and suitability. From their network of associates, Manpower will provide 6-week part-time work placements of up to 16 h per week (as participants receiving work assessment allowance (*Arbeidsavklaringspenger*) may have limits on how much they are allowed to work). Once a placement is arranged, the case manager, the participant, and the placement manager will meet to agree on a return-to-work plan and discuss whether any work accommodations are needed to overcome identified obstacles to returning to work [19, 20]. While Manpower aims to provide all of our placements, we may approach additional placement providers if needed.

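### The fallback design effect of 1.11 does not follow from unchanged assumptions, so the reduced total of 190 rests on a caseload or uptake that the protocol does not state

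*Protocol article*

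**What the plan says.** All figures are in the protocol article, Sample size {14}, unless noted.

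- Effect: "detecting a difference of 20% between the intervention group and the remaining cohort", with "Assuming a cohort return to work rate as high as 10" per cent, so 10% against 30%.
- Error rates: "with a power of 80% and a 5% significance level". Statistical methods {20a} adds "All tests will be two-sided".
- Base size at 1:3: "we will need data on 176 participants (132 control and 44 intervention").
- Inflation: 20% loss to follow-up, then clustering by case manager in the intervention arm only, with an ICC of 0.01 and "smallest cluster size of 7 and largest of 16, and so a design effect of 1.14". The recruitment target is 228.
- Fallback: if too many people decline the offer to fill the group sessions, allocation may become balanced and the target falls to 190, because "with the same assumptions the estimated design effect will be 1.11 in this case".
- Staffing, Intervention description {11a}: "we will train two to four people with prior experience of working with pain patients". No section adds managers if the allocation changes.
- Participant timeline {13}: a case manager is assigned to those who wish to join the intervention.

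**The concern.** The clusters are case managers. Moving from one intervention participant per three controls to equal arms puts more people into the intervention, yet the design effect falls. If the cluster sizes are really unchanged, the design effect cannot move. If the number of managers is unchanged and uptake is held fixed, each manager carries more people and the design effect must rise. Neither reading yields 1.11.

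The section authorises in advance a cut in the recruitment target from 228 to 190 during the trial. If the design effect behind 190 is too favourable, the switch would be made on a power statement that the trial's own inputs do not support.

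**Working it through.** **1. Reproducing the protocol.** Two proportions, 10% v 30%, two-sided 5%, 80% power, continuity-corrected formula:

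- 1:3: 43.6 in the intervention arm, so 44 and 132, total 176 as stated.
- Balanced: 71.2, so 72 per arm.
- 1:3 total: 132/0.8 + 44 × 1.14/0.8 = 165 + 62.7 = 227.7, so 228.
- Fallback total: 72/0.8 + 72 × 1.11/0.8 = 90 + 99.9 = 189.9, so 190.

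Without the continuity correction the base sizes would be 150 and 124, so the correction was used. The recruited intervention arm is about 63 at 1:3 and about 100 in the fallback (about 80 analysed).

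**2. Cluster sizes unchanged.** The design effect stays 1.14 and the fallback total is 72/0.8 + 72 × 1.14/0.8 = 90 + 102.6 = 192.6, so 193.

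**3. Number of managers unchanged, whole arm clustered.** DE = 1 + (m − 1) × 0.01, with m equal to 80 (analysed) or 100 (recruited) divided by the number of managers. Power is for 72 controls against 80/DE intervention participants.

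| Managers | People per manager | DE | Power at 190, corrected | Power at 190, uncorrected |
|---|---|---|---|---|
| 4 | 20–25 | 1.19–1.24 | 79.1–78.2% | 84.8–84.1% |
| 3 | 26.7–33.3 | 1.26–1.32 | 77.9–76.8% | 83.9–83.0% |
| 2 | 40–50 | 1.39–1.49 | 75.7–74.1% | 82.1–80.8% |

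Every caseload exceeds the stated maximum of 16. Letting clusters grow with the arm, the total needed for 80% by the corrected formula is 199–205 with four managers, 208–218 with three and 230–252 with two.

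**4. What 1.11 would need.** 1 + (m − 1) × 0.01 = 1.11 gives m = 12. That is six managers for 72 people, or four managers for 4 × 12 = 48 people. Forty-eight is 60% of the 80 analysed.

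**5. The 1:3 plan.**

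- Four managers: 44/0.8 = 55 people split 7, 16, 16, 16 give a sum of squares of 817, so DE = 1 + (817/55 − 1) × 0.01 = 1.1385, which rounds to 1.14. With equal clusters of 50 to 63 people, corrected power at 228 is 80.8–80.1%.
- Three managers: 7 + 16 + 16 = 39, below the 44 needed before any inflation. With equal clusters, DE is 1.16–1.20 and power 79.8–78.8%.
- Two managers: 7 + 16 = 23. With equal clusters, DE is 1.24–1.31 and power 77.9–76.4%.

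**The case against.** **Uptake.** The strongest reply is that clusters consist of people who accept, not of everyone allocated. Decliners have no case manager, and the fallback is triggered precisely by high refusal. At 60% uptake with four managers, m = 48/4 = 12 and the design effect is 1.11. With the 32 decliners unclustered, the effective intervention size is 48/1.11 + 32 = 75.2 against 72 required, and corrected power is about 81%. This stands as a possible explanation, and it means that 1.19–1.49 should not simply replace 1.11. It does not rescue the sentence. At 1:3, 1.14 with four managers needs 15 × 4 = 60 of 63 recruited, or all 55, to be clustered. The fallback would need about half of those recruited (48 of 100). That is a changed assumption, and the section inflates the whole arm in both cases.

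**Method and staffing.** The cited source for the design effect is not at hand, and the authors may have used a formula for unequal clusters. If the standard deviation is taken as a quarter of the range (an assumption), a mean of 11.5 gives 1.11 and a mean of 14.7 (44/3) gives 1.14. The mean caseload must still differ between the two scenarios. Strategies to improve adherence {11c} also lets trained working group members stand in for case managers, so four is not an absolute ceiling. That is cover if needed, not a planned increase.

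**Readings that go too far.** A reader might infer that the staffing plan contradicts the whole calculation, including 1.14 and 228. It does not: four managers lie within the planned range and reproduce 1.14. A reader might also infer that 190 cannot deliver 80% power. That is too strong. The shortfall with four managers is 1 to 2 points by a conservative formula, the planned analysis is a mixed logit model rather than a continuity-corrected test, and uncorrected power is at least 80.8% in every row above.

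**Conclusion.** The point holds for the fallback design effect. As written, 1.11 is inconsistent with the claim of unchanged assumptions. It requires more managers than planned or an unstated uptake of roughly half to 60%.

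The consequence is modest. On unchanged cluster sizes the target moves by three people, from 190 to 193. On unchanged staffing with the whole arm clustered, corrected power at 190 falls 1–2 points below 80% with four managers, 2–3 with three and 4–6 with two. These figures assume equal clusters in the fallback, an ICC of 0.01 and a manager for everyone allocated. They do not address dilution of the effect by refusal, which is a separate matter.

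At 1:3 the plan is sound with four managers. With two or three, the 7-to-16 range cannot hold and corrected power is about 76–80%.

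**What to change.** In Sample size {14}, give for each allocation the number of case managers, the assumed uptake and the resulting mean cluster size. Recompute the fallback design effect from these, and restate either the total that matches 80% power or the power that 190 delivers. If 1.11 rests on lower uptake or more managers, say so and remove the statement that the assumptions are the same. For 1:3, note that the 7-to-16 range and 1.14 presuppose four managers.

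The cost is a rewrite of a few sentences. The restated fallback figure may be slightly less favourable. Restating the power requires no additional participants; choosing to hold 80% may raise the fallback target.

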### Recruitment {15}

Over an anticipated recruitment period of 1 year, we will mount an advertising campaign across social media, pain groups, and charities (including pain and rheumatological charities: *Ryggforeningen*, *Norsk Revmatikerforbund*, *Foreningen for Kroniske smerter*), public facilities, and *Frisklivssentralene* (i.e. ‘healthy living’ centres, which provide help with health and work matters). Manpower will aid recruitment using its online channels. We will offer NOK 200 of high street vouchers to those joining the cohort, which we have previously found to help recruitment [60, 61].

### Assignment of interventions: allocation

#### Sequence generation {16a}

Randomisation will feature minimisation and be automated using a mix of Stata scripting (StataCorp, College Station, TX) and bash programming to keep personal data encrypted. The research team developed the minimisation script which at its core features the Stata program rct_minim [62, 63]. The first participant is randomly allocated with equal probability, and then for each subsequent participant, there is a two-thirds probability that allocation will be to the group that best minimises the imbalance on the selected factors (i.e. gender on three levels (male, female, or prefer not to say) and three levels of age (18 to 29, 30 to 49, and 50 and over)) [64–66].

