### Participant timeline {13}

A participant timeline was created according to the SPIRIT guidance and is presented in Fig. 3 [58]. Following admission to the cohort study, baseline measurement will be completed. After baseline measurement, one in three will be randomly selected to be invited to the intervention (see SPIRIT item 16a). If wishing to join the intervention, the participant will be assigned a case manager who will conduct the initial assessment. The case manager will then match the participant to a suitable work placement in collaboration with Manpower. The participant, case manager, and placement supervisor will agree and sign a return to work plan, and the participant will attend a 2-day work familiarisation session prior to the 6-week placement. Self-reported follow-up questionnaires will be completed by all participants 3, 6, and 12 months after baseline.

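### Read for the two groups the protocol compares, the stated minimisation rule allocates about 1:1, not the one in three or 132:44 the plan calls for

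*Protocol article*

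**What the plan says.** Three parts of the protocol article bear on the allocation ratio.

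- **Offer rate.** The Abstract, Trial design {8}, the consent section {26a} and Participant timeline {13} all describe one in three. The timeline says: "After baseline measurement, one in three will be randomly selected to be invited to the intervention".
- **Sample size {14}.** It uses a 1:3 ratio: "we will need data on 176 participants (132 control and 44 intervention". After inflation the target is 228. Balanced randomisation appears only as a possible later switch, with a different total of 190. Who will be blinded {17a} likewise treats 1:3 as visibly unequal and speaks of balanced groups only after that switch.
- **Sequence generation {16a}.** "The first participant is randomly allocated with equal probability". For each later participant, "there is a two-thirds probability that allocation will be to the group that best minimises the imbalance on the selected factors". The factors are gender and age, each on three levels. The section mentions no ratio.

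**The concern.** A coin that starts at one half and then favours whichever group reduces imbalance treats both groups alike. Such a rule balances the groups. Read plainly, the operative allocation text therefore describes the protocol's fallback design and not its main one.

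At stake are the number of people offered the intervention, the load on the two to four case managers planned in Intervention description {11a}, the number of placements to be found, and the cluster sizes of 7 to 16 on which the 1.14 design effect rests. The data monitoring and steering committees also could not check achieved arm sizes against the stated rule.

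**Working it through.** **1. Reproduce the planned arm sizes.** Inputs from Sample size {14}: cohort rate 10%, "detecting a difference of 20% between the intervention group and the remaining cohort" (so 30% against 10%), "with a power of 80% and a 5% significance level", three controls per intervention participant. From Statistical methods {20a}: "All tests will be two-sided".

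With r = 3, d = 0.20 and pooled rate (0.30 + 3 × 0.10)/4 = 0.15:

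- Uncorrected intervention arm: n′ = [1.96 √(4 × 0.15 × 0.85) + 0.8416 √(3 × 0.30 × 0.70 + 0.10 × 0.90)]² / (3 × 0.04) = 37.2.
- With continuity correction: n = (n′/4) × [1 + √(1 + 8/(n′ × 3 × 0.20))]² = 43.6, so 44 intervention and 132 control. This matches the plan's 176.
- Inflation: (132 + 44 × 1.14)/0.8 = 165 + 62.7 = 227.7, so 228. This also matches.
- Fallback: a 1:1 calculation gives 72 + 72, and (72 + 72 × 1.11)/0.8 = 189.9, so 190. The fallback labelled 1:2 is therefore truly balanced.

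**2. Offers needed among 228.** One in three: 228/3 = 76. A plain one in four: 228/4 = 57. The inflated 132:44 plan: about 63.

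**3. Offers under the stated rule, two groups.** By symmetry the expected share is one half, or 114. Simulation of 228 participants (1,500 runs; assumed frequencies: gender 35/63/2%, age 15/50/35%) gave a mean of 114 with a 95% range of 110 to 118. No run gave 76 or fewer. The one-half result does not depend on the assumed frequencies. The excess is 114/76 = 1.5, 114/63 = 1.8 or 114/57 = 2.0 times.

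**4. Ratio-weighted imbalance, same two-thirds coin.** The text does not state this, but it is a charitable reading.

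| Target | Needed | Mean offered (95% range) |
|---|---|---|
| One in three | 76 | 84 (77 to 94) |
| One in four | 57 | 78 (66 to 91) |

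With two groups every later participant has at least a 1/3 chance of the intervention, so the expected number is at least 0.5 + 227/3 = 76.2. One in four is then out of reach on average. Even at a constant 1/3, the binomial probability of 57 or fewer offers is 0.004.

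**5. More than two equal slots.** If the remaining 1/3 is shared among the other slots and all but one slot are pooled as control, symmetry gives 228/3 = 76 for three slots and 228/4 = 57 for four. Simulation agreed (76 and 57). The 1/3 floor in step 4 does not apply here: with three slots, a participant for whom the intervention slot is not preferred has a 1/6 chance of it.

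**6. Power.** By the uncorrected normal formula, 132:44 gives 0.855 and 88:88 gives 0.919, at the same total of 176.

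**7. Cluster size.** With four case managers, 63/4 = 15.75 fits under the assumed maximum of 16, while 114/4 = 28.5 does not if everyone accepts. The maximum is passed once more than 64 of 114 (56%) accept.

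**The case against.** The strongest reply is that the section never says how many groups the code minimises over. Its wording fits three equal slots as well as two, and step 5 shows that three or four slots deliver the intended ratios without changing a word. The protocol's label of 1:2 for a balanced fallback hints that 1:3 may have been meant as one of three. The code is not shown, and an article commonly leaves such settings to a fuller document. This stands: the documents do not show that the code is wrong. It does not clear the text, because the slot device is nowhere described and the protocol compares two groups throughout.

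Three stronger readings are tempting and are not supported:

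- **That the trial cannot deliver one in three.** This holds only for exactly two groups, and only for the rule as written.
- **That power suffers.** Balance raises it (step 6).
- **That the ratio would have to be changed ad hoc during recruitment.** The only switch described is stated in advance and is prompted by too few people for the group sessions.

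The effect on case managers also depends on uptake. The plan itself contemplates a balanced design, though for the case where many decline.

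**Conclusion.** The point holds as a contradiction in the text. Read for two groups, Sequence generation {16a} gives about 114 offers of 228, which is 1.5 times one in three, 1.8 times the inflated sample-size plan and 2 times a plain one in four. Ratio-weighting with the same coin narrows the gap but does not close it. This is more than missing detail, because the stated rule, read plainly, produces the balanced design that the protocol reserves as a fallback.

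The conclusion assumes two groups and the probabilities as printed. Whether the code shares the problem cannot be told from the document. The consequence is operational (offers, case-manager load, placements, cluster size) and concerns verifiability; it is not a loss of power.

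**What to change.** 1. **Settle one target ratio.** One in three is 1:2 and 132:44 is one in four; these conflict, and the fix cannot be specified until one is chosen. Then use one notation throughout, including for the balanced fallback.
2. **Simulate the live code** at 228 participants and compare the number offered with the target.
3. **Rewrite Sequence generation {16a} with a ratio-preserving rule**, stating the number of groups, weighting and probabilities. Either option works:
   - Equal slots, three or four, with one labelled intervention and the rest pooled as control.
   - Ratio-weighted imbalance with arm-specific probabilities. For one in three: 1/3 for the first participant and ties, 2/3 to intervention when it is preferred, 5/6 to control when control is preferred. When intervention is preferred one time in three, the share is 1/3 × 2/3 + 2/3 × 1/6 = 1/3; simulation gave 76 (74 to 79). For one in four: 1/4, 2/3 and 8/9, with 1/4 × 2/3 + 3/4 × 1/9 = 1/4; simulation gave 57.
4. **Correct the code if it matches the current text.** Trial status gives recruitment from January 2023, so record the date of any change and account for the before and after periods in the analysis.

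The cost is a few lines of code or text and no extra participants.
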